Nine-month isoniazid (INH) monotherapy (9H) is a standard TPT regimen recommended by the WHO. However, its effectiveness is limited by poor treatment complicance, partly owing to the long duration of the regimen. WHO recommended a 3-month regimen of weekly rifapentine (RFT) and INH (3HP) as an alternative ^[5]^. However, the safety profile of 3HP in Chinese population raises concerns ^[6]^.

Due to the high clinical heterogeneity, complex disease conditions and medications in RDs patents, the high-quality studies on TPT in this population is very limited. Considering the high risk of ADRs due to existed organ damage and concomitant medication which is almost inevitable in RDs patients, TPT regimens should be selected with caution. Based on previous studies and clinical experience from our center, we modified the 3HP regimen to 3HP-PUMCH, which involves twice weekly RFT at 450mg and daily INH at a maximum dose of 300mg for 3 months. We evaluated the efficacy, safety and completion of 3HP-PUMCH compared to the standard 9H regimen in high-risk RDs patients with LTBI.

1. **Objectives**
   1. To determine the non-inferiority of the 3HP-PUMCH regimen compared to the standard 9H regimen in preventing ATB in high-risk RDs patients with LTBI.
   2. To compare the safety profile and treatment completion rates between the two regimens.
2. **Methods**
   1. **Study design**

The study is a multi-center, open-label, non-inferiority, randomized controlled trial.

- 1. **Study population**
     1. Eligible criteria

1. Aged 18-70 years;
2. Diagnosed with at least one of the high-risk RDs including systemic lupus erythematosus (SLE), Takayasu's arteritis (TA), Behcet's disease (BD), primary Sjogren's syndrome (SS), rheumatoid arthritis (RA) and ankylosing spondylitis (AS);
3. Not currently using biologics;
4. Taking any of the following medications: ①≥15mg daily of prednisone or equivalent; ②at least one of the following immunosuppressive agents: methotrexate (MTX), cyclophosphamide (CTX), mycophenolate mofetil (MMF), cyclosporine A (CsA), azathioprine (AZA), tacrolimus (FK-506), leflunomide, iguratimod and tripterygium wilfordii; ③initiating TNF inhibitors treatment.
5. Positive for blood T-SPOT.TB (≥24 SFCs/10^6^ PBMC).
   - 1. Exclusion criteria:
6. Suspected or confirmed ATB,
7. Seropositive status for HIV-Ab,
8. Seropositive status for HCV-Ab or HBV surface antigen,
9. Severe liver damage (total bilirubin > 3mg/dL or aminotransferase > 2ULN) or liver cirrhosis,

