10. Prior use of TPT,
11. History of allergy to INH or RFT,
12. Pregnancy or lactation.
    1. **Randomization**

Participants were randomly allocated in a 1:1 ratio into the 9H and 3HP-PUMCH groups using a computer-generated random sequence. Randomization was stratified in the research center. A random sequence was generated using a fixed-block randomization method with a block length of 4. Allocation concealment was maintained using a web-based central randomization system.

- 1. **Interventions**
     1. Experimental Group

3HP-PUMCH regimen: INH once daily, 5 mg/kg (with a maximum daily dose of 300 mg), combined with RFT twice a week, 450 mg each time, for 3 months.

- - 1. Control Group

9H regimen: INH once daily, 5 mg/kg (with a maximum daily dose of 300 mg), for 9 months.

- - 1. Concomitant Treatment

RDs Treatment: The patient's baseline RDs treatment was followed according to the best available clinical guidelines/consensus and adjusted as needed by the treating clinician. A uniform RD treatment regimen was not stipulated.

- 1. **Outcomes**
     1. **Primary outcomes**

The occurrence of ATB up to the end of the follow-up period (24 months after randomization).

1. Diagnosis criteria:

- Microbiologically confirmed ATB: Biological specimens were positive by smear microscopy, culture, Xpert MTB/RIF, or other molecular biological diagnostic methods.
- Clinically diagnosed ATB: A clinical diagnosis of ATB was made when patients present characteristic symptoms (e.g., fever, cough, chest pain, night sweats, weight loss), supported by highly suggestive laboratory and imaging findings. Additionally, the diagnosis must be corroborated by a positive response to empiric TB treatment.

1. Diagnosis Adjudication:

All suspected ATB cases were reviewed by an external Endpoint Event Adjudication Committee (comprising two TB and one rheumatology experts) who were blinded to the TPT regimen allocation.

- - 1. **Secondary outcomes**

1. Permanent discontinuation of TPT due to serious adverse events (SAEs) or ATB occurrence.
2. ADRs related to prophylactic drugs (assessed by WHO-UMC causality criteria).
3. Completion rate of TPT.

Completion of treatment are defined as the consumption of at least 22 doses of RFT and at least 81 doses of INH within 16 weeks for the 3HP-PUMCH group, and 243 doses of INH within 52 weeks for the 9H group.

- 1. **Data collection and follow up**
     1. **Data collection:**

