8. Sensitivity Analysis Set (PP): The Per-Protocol (PP) analysis set includes all participants from the mITT set who completed the TPT.
   - 1. Statistical Methods
9. Primary Outcome Analysis

- The cumulative incidence and its 95% CI will be estimated using the Exact Method.
- Non-inferiority will be concluded by comparing the upper bound of the 95% CI for the difference in cumulative incidence with the pre-set non-inferiority margin (1.4%).
- Non-Inferiority Test Criteria: If the upper bound of the 95% CI is < 1.4%, non-inferiority will be considered demonstrated.
- Superiority Test: If non-inferiority is achieved, a further assessment will be made to determine whether the upper bound of the 95% CI is < 0.0% to test for superiority.

1. Secondary Outcome Analysis

Descriptive statistical methods will be used. The rates of adverse drug reactions (ADR), liver toxicity, and other outcomes will be compared using chi-square tests, and 95% CIs will be calculated.

1. Sensitivity Analysis

In the mITT population, incidence rates per person-year will be calculated, and the difference in incidence rates and its 95% CI will be estimated.

1. Software

Analysis will be conducted using R software (version 4.4.1).

1. **Monitoring and Oversight**

The trial is overseen by a Coordinating Center (Peking Union Medical College Hospital). An external Endpoint Event Adjudication Committee is established to independently review and validate all primary outcome events (ATB), ensuring objectivity and consistency.

1. **Ethics and Dissemination**
   1. **Research Ethics Approval**

This study received approval from the Ethics Committees of the participating hospitals (Approval Number: JS-1498). All procedures comply with the ethical standards of the institutional and national research committees and with the Helsinki declaration.

- 1. **Informed Consent**

All participants provided written informed consent prior to enrollment in the study.

- 1. **Protocol Amendments**

Any substantial changes to the protocol will be submitted to the Ethics Committees for approval and will be updated in the trial registry (ChiCTR).

- 1. **Dissemination Policy**

The results of this study will be published in peer-reviewed journals (such as this manuscript) and presented at scientific conferences. The final protocol will be accessible to readers as supporting information accompanying the main manuscript. All authors meet the criteria for authorship.

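### Randomisation is stratified by centre but the secondary comparisons are plain chi-square tests, which are slightly conservative if completion or ADR rates differ between centres

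*Protocol*

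**What the plan says.** Section 3.1 describes the design: "The study is a multi-center, open-label, non-inferiority, randomized controlled trial". Section 3.3 sets the allocation: "Participants were randomly allocated in a 1:1 ratio into the 9H and 3HP-PUMCH groups". It then states that "Randomization was stratified in the research center", using a "fixed-block randomization method with a block length of 4". The number of centres is not given.

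Section 3.5 lists the secondary outcomes: permanent discontinuation of preventive treatment, "ADRs related to prophylactic drugs (assessed by WHO-UMC causality criteria"), and "Completion rate of TPT". No expected rate is given for any of them.

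The paragraph on secondary outcome analysis in section 3.7 opens with "Descriptive statistical methods will be used". It then names ADRs and continues: "liver toxicity, and other outcomes will be compared using chi-square tests, and 95% CIs will be calculated". Completion is not named there and falls under the other outcomes. No stratified test or centre adjustment is mentioned, and the method for the intervals is not stated.

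**The concern.** Small blocks within centre keep the two arms nearly equal in every centre, so centre differences in outcome largely cancel from the comparison between arms. A chi-square test on the pooled two-by-two table does not use this. Its variance is that of a trial randomised without regard to centre.

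The protocol gives some reason to expect centre differences in these outcomes. Background rheumatic treatment is left to the treating clinician, the trial is open-label, and the blinded external committee reviews suspected ATB only, not ADRs. This makes centre variation plausible but does not show it.

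At stake is a little precision on the second objective in section 2, the comparison of safety and completion. For safety, a conservative test is not the cautious choice, because it makes a real ADR difference slightly harder to detect.

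**Working it through.** **Stated figure.** The only planning figure is the primary sample size. With rates of 3.6% and 1.1%, a margin of 1.4%, one-sided alpha 0.025 and 80% power:

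- variance sum = 0.036 × 0.964 + 0.011 × 0.989 = 0.0456
- n = (1.960 + 0.842)² × 0.0456 / (0.014 + 0.025)² = 235.2, rounded up to 236 per group
- 236 / 0.9 = 262.2, rounded up to 263 per group, 526 in total

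This reproduces the protocol and is not affected by the present point. No figure is stated for the secondary comparisons, so what follows rests on assumed ranges.

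**Formula.** With equal centres, balanced arms within centre and, for simplicity, the same centre rates p in both arms, the pooled variance splits as

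p̄(1 − p̄) = mean of p(1 − p) + between-centre variance of p.

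The stratified analysis keeps only the first term. The share removed is 1 − mean[p(1 − p)] / [p̄(1 − p̄)], and the interval width changes by the square root of the remaining ratio.

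**Numbers.** Five equal centres are assumed, with 263 per arm. Half-width = 1.96 × √(2 × variance / 263).

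| Assumed centre completion rates | Mean p(1−p) | p̄(1−p̄) | Variance cut | Width ratio | Half-width, pooled | Half-width, stratified | Saving |
|---|---|---|---|---|---|---|---|
| 70, 75, 80, 85, 90% | 0.1550 | 0.80 × 0.20 = 0.1600 | 3.1% | 0.984 | 6.84 points | 6.73 points | 0.11 points |
| 60, 70, 80, 90, 95% | 0.1495 | 0.79 × 0.21 = 0.1659 | 9.9% | 0.949 | 6.96 points | 6.61 points | 0.35 points |
| No difference between centres | equal | equal | 0% | 1.000 | – | – | nil |

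A variance figure makes the gain look larger than it is. A cut of 3.1% or 9.9% in variance is 1.6% or 5.1% in interval width.

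**General form.** If ICC is the share of outcome variance lying between centres, the width ratio is √(1 − ICC), and the true two-sided level of the pooled test at nominal 0.05 follows:

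- ICC 0: ratio 1.000, level 0.050
- ICC 0.01: ratio 0.995, level 0.049
- ICC 0.05: ratio 0.975, level 0.044
- ICC 0.10: ratio 0.949, level 0.039

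**Simulation.** Settings: 526 participants, ten equal centres (assumed), no treatment effect, rates of 10%, 30% and 80%, ICC from 0 to 0.10, 6,000 runs each.

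- At 80%, the half-width was 6.80 points pooled against 6.65 stratified at ICC 0.05, and 6.77 against 6.47 at ICC 0.10.
- At ICC 0 the stratified interval was no narrower (ratio 1.002).
- Across all settings the chi-square test rejected in 3.9% to 5.2% of runs, and the pooled interval covered in 94.7% to 96.1%.
- The Cochran-Mantel-Haenszel test rejected in 4.8% to 5.4%. Simulation error at 5% is √(0.05 × 0.95 / 6,000) = 0.3 points.

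**The case against.** The strongest reply is that an unadjusted chi-square test is valid here. It keeps its level, the analyses are labelled descriptive, no power or decision rule hangs on them, and the saving is a fraction of a percentage point. All of that stands, and it keeps the point minor. It does not remove it, because comparing safety and completion is a stated objective and the same paragraph goes on to specify tests.

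A second reply is that adjustment for stratification factors is usually left to the SAP, which is not shown. This holds for the intervals: a chi-square test does not determine how a confidence interval is built, so it is only an inference that the intervals ignore centre. It does not hold for the test, which the protocol names.

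A reader might infer that the intervals for completion and ADRs are in fact too wide. The documents do not support this. They give no centre-level rates, no number of centres and no expected secondary rates, and with no centre variation the gain is nil.

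A reader might also infer that the primary ATB analysis should be stratified. At the planned rates, 236 × 0.036 + 236 × 0.011 = 8.5 + 2.6, or about 11 events, are expected in total. Many centres could have none, and the gain would be close to nil.

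**Conclusion.** The protocol fixes a test that does not use the strata in which it randomises. This is a modest loss of efficiency, not an error of inference. If completion or ADR rates differ between centres, the stated tests, and any intervals built the same way, are slightly conservative: about 1.6% to 5% of interval width, or roughly 0.1 to 0.35 percentage points of half-width near 80% completion. Those figures rest on assumed ranges of 70-90% and 60-95% across five equal centres, with arms balanced within centre. The loss is nil if rates do not differ, and type I error is not inflated. A change of this size is unlikely to alter a conclusion. The case for acting is that a method matched to the design is available almost free.

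**What to change.** In the secondary outcome paragraph of section 3.7, replace the chi-square tests by wording to this effect: *Completion, ADRs, liver toxicity and permanent discontinuation will be compared by Cochran-Mantel-Haenszel tests stratified by centre, and reported as Mantel-Haenszel risk differences with 95% CIs stratified by centre.* This also settles how the intervals are built.

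Add a rule for pooling very small centres, based on numbers enrolled and not on outcomes, and fix it before the arms are compared. That rule is the one real cost, since the pooled test needs no such choice. Otherwise the change is a sentence of text, because centre is already held for the randomisation. With 1:1 blocks of four, the Mantel-Haenszel weights are nearly proportional to centre size, so the point estimates should barely move. Sample size and the primary analysis stay as they are.

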Patient data will be collected by trained researchers using a standardized case report form (CRF). At baseline, demographic characteristics, diagnosis and course of RDs, current medication use (including glucocorticoids and/or immunosuppressants), and a series of laboratory tests will be conducted to assess participants' general health. These tests will include hematological parameters, liver and renal function, inflammatory markers, and fasting blood glucose.

- - 1. **Follow-up procedures:**

Participants in the 3HP-PUMCH group will attend outpatient follow-up visits at their recruitment center at months 1, 2, and 3 during preventive treatment. At each visit, clinical assessments and laboratory tests, including hematological parameters and liver and renal function tests, will be conducted. Medication adherence and adverse events will be documented, with particular attention to any drug-related side effects. After completing TPT, participants will return for follow-up visits at months 6, 12, 18, and 24 to assess the incidence of ATB.

Participants in the 9H group will attend outpatient follow-up visits at months 1, 2, 3, 6, and 9 during preventive treatment. The same set of clinical and laboratory assessments, as well as monitoring for medication adherence and adverse events, will be performed. Post-treatment visits will also be conducted at months 6, 12, 18, and 24 to record any incidence of ATB.

- - 1. **Medication adherence assessment**

Medication adherence will be evaluated using the 8-item Morisky Medication Adherence Scale (MMAS-8). The MMAS-8 is a self-reported questionnaire that categorizes adherence as high, medium, or low based on the total score. Assessments will be conducted at each follow-up visit during preventive treatment.

- 1. **Statistical Considerations**
     1. **Sample Size Calculation**

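### Section 3.7 compares liver toxicity by an unadjusted chi-square test although baseline liver function is recorded for everyone; the test is valid but probably gives up a little precision

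*Protocol*

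**What the plan says.** Under Secondary Outcome Analysis, section 3.7 first states that "Descriptive statistical methods will be used". It then fixes the comparison of ADRs and liver outcomes: "liver toxicity, and other outcomes will be compared using chi-square tests", with 95% CIs. It names no covariate.

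Section 3.6 lists the baseline laboratory work: "These tests will include hematological parameters, liver and renal function, inflammatory markers, and fasting blood glucose". Section 3.2 excludes only "Severe liver damage (total bilirubin > 3mg/dL or aminotransferase > 2ULN) or liver cirrhosis", so a participant may enter with an aminotransferase anywhere up to 2 x ULN. This criterion also means that aminotransferase has to be known at entry.

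The second objective is to compare the safety and completion of the two regimens. The Background gives existing organ damage as one reason to expect more ADRs in these patients. Section 3.5 defines the related secondary outcome as "ADRs related to prophylactic drugs (assessed by WHO-UMC causality criteria". Liver toxicity as such is named only in section 3.7, without a threshold.

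**The concern.** If liver toxicity is judged by a peak value above a fixed multiple of ULN, a participant who starts near 2 x ULN is closer to being counted than one who starts at 0.5 x ULN. Baseline ALT is then prognostic for the outcome. An unadjusted comparison leaves that predictable variation in the standard error, whereas a standardised estimate from a model containing the baseline value removes part of it.

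What is at stake is the width of one safety interval. The protocol treats liver risk as important enough to restrict entry and to measure at every on-treatment visit, so a narrower interval has some value. The primary comparison is not affected.

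**Working it through.** **The protocol's own figure.** The only calculated figure is the sample size for active tuberculosis. With 3.6% v 1.1%, a margin of 1.4 points, 80% power and one-sided 0.025:

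n = [0.036 x 0.964 + 0.011 x 0.989] x (1.960 + 0.842)² / (0.014 + 0.025)² = 235.2, so 236 per group.

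236 / 0.9 = 262.2, so 263 per group and 526 in total. Both figures reproduce, and neither depends on how liver toxicity is analysed. No figure is stated for the safety comparison.

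**Inputs for the check.**
- From the protocol: 263 randomised per arm (236 after attrition), 1:1 allocation, entry truncated at 2 x ULN, unadjusted test.
- Assumed, because the protocol does not give them: toxicity defined by a fixed multiple of ULN; toxicity rate 4% to 15%; correlation of log baseline with log peak ALT 0 to 0.6.

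**Crude interval.** Half-width = 1.96 x sqrt{[p1(1-p1) + p2(1-p2)] / n}, with n = 263 per arm:
- 4% in both arms: 1.96 x sqrt(0.0768 / 263) = 3.35 points.
- 15% in both arms: 1.96 x sqrt(0.2550 / 263) = 6.10 points.
- 10% v 5%: 1.96 x sqrt(0.1375 / 263) = 4.48 points.

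**Effect of adjustment, by formula.** If the covariate explains a share R² of the outcome variance, the large-sample half-width is multiplied by sqrt(1 - R²). For 10% v 5% it goes from 4.48 to 4.37 points at R² = 5% and to 4.25 points at R² = 10%.

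**Effect of adjustment, by simulation.** 263 per arm, baseline ALT truncated at 2 x ULN. The crude risk difference is compared with the standardised risk difference from a logistic model containing treatment and log baseline ALT only:

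| Correlation, baseline to peak | Change in CI width |
|---|---|
| 0 | about +0.3% |
| 0.3 | 0 to -2% |
| 0.5 | -2 to -6% |
| 0.6 | -5 to -10% |

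In points, for 10% v 5%, the half-width of 4.48 becomes 4.39 (x 0.98) to 4.21 (x 0.94) at a correlation of 0.5. At the most favourable end it becomes 4.03 (x 0.90).

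**What happens when the covariates are weak.** A separate simulation used 236 per arm, event rates from 10% v 5% to 30% v 20%, and one baseline covariate of varying strength plus four uninformative ones:
- Discrimination (AUC) 0.50: interval 0.5% to 1.1% wider.
- AUC about 0.60: between 0.2% wider and 0.6% narrower.
- AUC about 0.68: 0.5% to 3.1% narrower.
- AUC about 0.74: 3.1% to 6.2% narrower.

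The gain therefore depends on the strength of the baseline value, and padding the model with weak covariates costs a little.

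**Scale.** Gains quoted as variance look about twice as large as gains in width. For example, an SD of the risk difference of 0.0315 crude and 0.0297 adjusted is 1 - (0.0297/0.0315)² = 11% in variance, but 1 - 0.0297/0.0315 = 5.7% in width. Width is what the reader of the safety table sees.

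**The case against.** The strongest reply is that nothing here is wrong. Under 1:1 randomisation a chi-square test with a 95% CI is a valid comparison of event rates. The section is introduced as descriptive, with no safety hypothesis, margin or power target, and an adjusted analysis may stand in a statistical analysis plan that is not shown. The validity of the test stands in full, which is why this is only an optional improvement. The point remains worth making because the protocol does fix a method here, and that method leaves a collected baseline value unused.

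The second reply is that the mechanism needs a threshold definition of liver toxicity, and the protocol states none. Under a definition relative to baseline, or one based on causality judgement, baseline ALT could matter much less. This also stands, and the gain is conditional on it.

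A reader might infer more than the protocol supports:
- **All ADRs.** The argument does not carry over. ADRs are judged by causality criteria, and nothing shows that baseline ALT predicts non-hepatic reactions.
- **Background drugs.** Section 3.6 does record "current medication use (including glucocorticoids and/or immunosuppressants" at baseline, but section 3.2 admits many drugs and combinations, so a drug grouping would first have to be defined. Section 3.4 adds that "A uniform RD treatment regimen was not stipulated" and lets treatment change after randomisation, so baseline drugs may not reflect exposure on treatment. Adjusting for later drugs could introduce bias.
- **Chance imbalance.** Imbalance in baseline ALT is sampling variation that the unadjusted interval already covers. It is no additional bias.
- **Participants saved.** The sample size is set by the tuberculosis comparison, so translating the gain into a number of participants has no practical meaning.

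**Conclusion.** The point holds for liver toxicity and baseline ALT only, as a small improvement in efficiency. The planned test is valid, and no statement in the protocol is contradicted. Under the assumed fixed threshold and 4% to 15% toxicity, adjustment changes the CI width by between about 0% and -10% over correlations of 0 to 0.6, and by about -2% to -6% at 0.5. With no correlation the cost is about 0.3% in width. Every one of these inputs is an assumption, because the protocol gives no toxicity rate, threshold or correlation. The size of the gain is therefore uncertain. That it is modest, with a negligible downside, is reasonably secure.

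**What to change.** In section 3.7, before outcomes are seen, add one sentence for liver toxicity: a logistic model with treatment and log baseline ALT, reported as the standardised (marginal) risk difference with its 95% CI, and the chi-square test kept as supportive. The standardisation step matters, because the treatment coefficient alone gives a conditional odds ratio and not the difference in rates. State the definition of liver toxicity that the model uses.

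The cost is a sentence and a few lines of R, with no new data. There is no gain if baseline ALT is weakly prognostic or events are very few. At 4% toxicity about 0.04 x 263 = 10.5 events per arm are expected, so the model should carry no further covariates.
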